## Abstract

**Background:**

Diabetic peripheral neuropathy (DPN) is the most common complication of diabetes mellitus with significant clinical sequelae that can affect a patient’s quality of life. Metabolic and microvascular factors are responsible for nerve damage, causing loss of nerve function, numbness, painful sensory symptoms, and muscle weakness. Therapy is limited to anti-convulsant or anti-depressant drugs for neuropathic pain and paresthesia. However, reduced sensation, balance and gait problems are insufficiently covered by this treatment. Previous data suggests that acupuncture, which has been in use in Traditional Chinese Medicine for many years, may potentially complement the treatment options for peripheral neuropathy. Nevertheless, more objective data on clinical outcome is necessary to generally recommend acupuncture to the public.

**Methods:**

We developed a study design for a prospective, randomized (RCT), placebo-controlled, partially double-blinded trial for investigating the effect of acupuncture on DPN as determined by nerve conduction studies (NCS) with the sural sensory nerve action potential amplitude as the primary outcome. The sural sensory nerve conduction velocity, tibial motor nerve action potential amplitude, tibial motor nerve conduction velocity, the neuropathy deficit score, neuropathy symptom score, and numeric rating scale questionnaires are defined as secondary outcomes. One hundred and eighty patients with type 2 diabetes mellitus will be randomized into three groups (needle acupuncture, verum laser acupuncture, and placebo laser acupuncture). We hypothesize that needle and laser acupuncture have beneficial effects on electrophysiological parameters and clinical and subjective symptoms in relation to DPN in comparison with placebo.

**Discussion:**

The ACUDIN trial aims at investigating whether classical needle acupuncture and/or laser acupuncture are efficacious in the treatment of DPN. For the purpose of an objective parameter, NCS were chosen as outcome measures. Acupuncture treatment may potentially improve patients’ quality of life and reduce the socio-economic burden caused by DPN.

**Trial registration:**

German Clinical Trial Register (DRKS), No. DRKS00008562, trial search portal of the WHO (http://apps.who.int/trialsearch/).

## Background

Diabetic peripheral neuropathy (DPN) is the most common complication of diabetes mellitus with significant clinical sequelae and impact on patients’ quality of life [1, 2]. DPN manifests itself on the toes and progresses in a stocking distribution [3]. Nerve damage is related to hyperglycemia. However, various other mechanisms play a role in the pathogenesis of DPN [3]. These include elevated polyol pathway activity, advanced glycation end products (AGEs), oxidative stress, growth factors, impaired insulin/C-peptide action, and elevated protein kinase C activity. These may directly affect neuronal tissues as well as vascular structures, thus compromising nerve vascular supply [4, 5].

Clinical manifestations include paresthesia, burning sensations, and neuropathic pain as well as negative symptoms like hypesthesia, hypalgesia, and pallhypesthesia. These may contribute to balance problems and unsteady gait, leading to falls [6] and an increased risk of bone fractures and hospitalization [7]. Motor symptoms, for example muscle spasm and weakness occur less frequently [3]. DPN is associated with an increased risk of ulceration and amputation of the lower extremities as well as increased healthcare costs [8–10]. Nerve damage can occur on the myelin sheath as well as at the axonal level [11]. Differentiation is achieved by nerve conduction studies (NCS) [12]. Whilst neuropathic pain and paresthesia can be palliated by anti-convulsants, tricyclic antidepressant drugs or serotonin-noradrenalin re-uptake inhibitors [13], pharmacologic management of decreased sensation is generally ineffective, thus forming a gap in treatment strategies.

During the last decades, acupuncture has become an empirical complementary treatment option for DPN. It is recommended by the World Health Organisation [14] and the National Institute of Health [15] but treatment effectiveness is still under debate. Reviews concerning acupuncture for peripheral neuropathy (PN) have found that, despite the majority of studies reporting positive results, a reliable statement of effectiveness is not possible due to methodological limitations [16–22]. Randomized controlled, blinded clinical trials of adequate statistical power and design are still pending.

Whilst acupuncture concepts using proximal or systemic acupuncture points on upper and lower extremities failed to show efficacy [23], our pilot studies using the selection of local and distal points described here showed promising results for the treatment of DPN, chemotherapy-induced PN and PN of unknown cause(s). These studies have verified the improvement that can be found in subjective scales by means of NCS parameters [24–27]. Acupuncture has been shown to increase blood perfusion towards the periphery of the limbs following needle insertion [28]. The results of our pilot studies were potentially related to the acupuncture effect on the blood flow through vasa nervorum and dependent capillary beds supplying the neurons [26]. These findings are encouraging for setting up the framework of a clinical study of adequate sample size using strict methodological standards.

### Definition of adequate controls for acupuncture

The development of appropriate designs for clinical acupuncture trials remains a methodological challenge. A major problem is the definition of placebo controls and blinding procedures, as the insertion of acupuncture needles is usually perceptible and visible.

Double-blinding of needle acupuncture has been achieved for immediate effects using invasive sham acupuncture concepts as control [29, 30]. However, this approach is problematic for long-term trials because of a possible overlap of specific as well as unspecific physiological and placebo effects. Sham acupuncture, at irrelevant or non-acupuncture points, was found to promote physiological stimuli due to an unspecific endorphin release in a range of 33–50%, exceeding the effect of a suggestive placebo therapy [31]. Hence, treatment with invasive sham acupuncture is not an inert placebo but an active treatment of unknown activity [32].

Accordingly, no reliable blinding methodology for needle acupuncture has been achieved so far for time spans of 10 weeks’ intervention. Differences in verum and placebo treatment patterns could not be accurately masked from the practitioner over time, creating the risk of bias [33].

Even shallow needling showed both specific and unspecific effects [34–36], evoking physiological responses similar to classical needle acupuncture and distorting the results [37].

To overcome these obstacles we include Laserneedle® acupuncture with multichannel red laser light into the ACUDIN study design. Laser needles are not inserted into the skin but merely placed on the surface of the acupuncture points; however, the therapeutic effects are of a similar dimension to those evoked by manual needle acupuncture [38]. The initial effect of laser acupuncture is mediated by the impact of ATP release from cutaneous mast cells [39, 40], which is considered comparable to the mechanical effect of needle acupuncture [41, 42]. Patients do not feel the activation of the laser needles as the radiation intensity is optimized for this purpose [43] and they cannot distinguish between verum and placebo laser [44]. Laser acupuncture is considered an appropriate means of control for acupuncture trials for evaluating the effect of needling per se [44].

## Methods/design

### Trial design

The aim of the ACUDIN trial is to examine if acupuncture and laser acupuncture have beneficial effects on NCS parameters, clinical scores and patient’s complaints in DPN as evaluated by standardized tests. A prospective, randomized, placebo-controlled, partially double-blinded, three-armed study design has been applied to the ACUDIN trial to compare the effects of classical needle acupuncture and laser acupuncture with those of placebo laser acupuncture.

Patients will receive 10 treatments over a period of 10 weeks. Each session will last 20 min. Neurological assessment, including NCS, is performed at baseline, week 6 and week 15 (Fig. 1).

**Fig. 1 Fig1:**
[figure not shown]
Depicts the ACUDIN trial protocol

### Trial personnel

A total of four persons are involved in the ACUDIN trial procedure. The treatment is performed by the following health professionals: (i) experienced practitioners who are members of a German Physicians Society for Acupuncture. They have completed a standardized training course, undertaken formal accreditation by examination and a period of supervised medical experience required for administering the acupuncture interventions and were trained by Laserneedle® specialists for the implementation of multichannel laser acupuncture; (ii) two study nurses are involved in the treatment procedure as described below; and (iii) experienced neurologists, not involved in further study procedures, perform neurological assessments including NCS.

### Study population

A total of 180 patients with DPN due to diabetes mellitus type 2 will be recruited from regional medical clinics, via the homepage of the operating institute, media reports, and advertisements.

### Inclusion criteria

Participants who meet the following conditions will be included:Male or female aged > 18 yearsConfirmed diagnosis of diabetes mellitus type 2 (i.e., HbA_1c_ ≥ c6,5% (48 mmol/mol)

[45] and/or on diabetes medication for more than 1 year)Stable levels of HbA_1c_ during the last 6 months (i.e., deviation < 1% (11 mmol/mol))Clinically confirmed diagnosis of DPNPathologic results in NCS (i.e., sural SNAP < 10 μV, sural NLG < 42 m/s, tibial MNAP < 8 mV, tibial MNLG < 40 m/s) [46]Naive to laser acupunctureNo prior acupuncture treatment for peripheral neuropathy

### Exclusion criteria

Participants who present one or more of the following conditions are excluded:PN caused by conditions other than diabetes (e.g., alcohol abuse, chemotherapy, hereditary causes, chronic inflammatory or idiopathic PN, and others)History of epilepsyCoagulopathy or use of anticoagulants with bleeding time > 3 min, prothrombin time < 40%, platelet count < 50.000/μl, or PTT > 50 sBacterial infection or other skin diseases at the lower extremities that impede acupuncture treatmentBone fracture of the lower extremities during the last 3 monthsUse of acupuncture during the last 3 monthsOpiate, analgesic, or drug abusePsychiatric illnesses other than mild depressionIncapacity in giving informed consent or in following the study instructions due to language disturbances, serious cognitive deficits, or lack of timePregnant or breast-feeding womenCurrent participation in other clinical studies

### Randomization procedure

Recruited patients are randomized in a ratio of 1: 1: 1 into three parallel treatment groups of 60 participants: (i) classical needle acupuncture, (ii) verum laser acupuncture, and (iii) placebo laser acupuncture. Randomization is prepared beforehand with 180 identical closed envelopes, each.

containing one of the three possible group allocations and a randomly generated four-number pseudonym code for further data processing. Randomization is performed by envelope lottery immediately prior to the first treatment session by study nurse 1. Patients and practitioners are only informed about the patients’ allocation to either needle or laser treatment. However, patients do not know whether they will receive a true treatment or placebo. Group assignment will not be exposed until the final data analysis report is completed.

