## Blinding

A single-blind design is performed for needle acupuncture because of the difficulties of practitioner blinding for the needling procedure as specified above. A double-blind design is performed for laser acupuncture. Caregiver blinding for laser acupuncture is achieved by dividing the treatment into three steps.i.practitioner fixes the laser needles without activating them;ii.study nurse 1 operates the laser device according to the randomization (verum or placebo);iii.study nurse 2 removes the laser needles after treatment.

Practitioners and study nurses do not communicate concerning the patients’ group allocation. Further, the investigator performing the neurological assessment and NCS does not know about the type of treatment given to the patient.

Regarding patients and the blinding procedure: the laser device is placed behind a folding screen so patients cannot see it. Patients wear laser protective glasses which make it impossible to perceive the laser light. They are informed that the laser device would emit visible and/or invisible laser beams and that the protection of the eyes is fundamental in any case because of the safety precautions as required by law. The laser needles are covered with a blanket. Acoustic functions of the laser device are deactivated prior to the study, so there is no difference between verum and placebo activation. This protocol will not be published in advance so patients cannot draw any conclusions concerning treatment allocations. Study participation is allowed only once.

For data transfer and processing, pseudonym codes are used in order to mask patient identity and treatment groups from outcome assessors and statisticians. The data is only matched after completion of statistical analysis.

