### Placebo laser acupuncture

Placebo laser acupuncture is performed as described for verum laser acupuncture with slight modifications. Study nurse 1 provides the same steps as for the verum treatment but without activating the laser, pressing an invalid point at the soundless touch screen of the laser device. Therefore, from the patient’s perspective, the procedure is identical to that used in the verum laser group.

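### The envelope lottery, run by the nurse who knows and gives verum or placebo laser, fixes no opening order, so adherence to the random draw cannot be verified.

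*Protocol article*

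**What the plan says.** Under Randomization procedure, patients are "randomized in a ratio of 1: 1: 1 into three parallel treatment groups of 60 participants". The material is described thus: "Randomization is prepared beforehand with 180 identical closed envelopes". The slip inside shows the treatment arm together with a random code that later serves as the patient's pseudonym. The draw itself is described as follows: "Randomization is performed by envelope lottery immediately prior to the first treatment session by study nurse 1".

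Under Blinding, study nurse 1 is also the person who operates the laser as randomized. The section Placebo laser acupuncture adds: "Study nurse 1 provides the same steps as for the verum treatment but without activating the laser". This nurse therefore knows which laser patients receive placebo. In the needle arm the practitioner inserts the needles, so the nurse's delivery role concerns the two laser arms only.

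The stated safeguards are a rule that "Practitioners and study nurses do not communicate concerning the patients’ group allocation", a neurological assessor who is unaware of the treatment, and pseudonym codes for data processing.

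**The concern.** A lottery has no prescribed order. The only identifier mentioned is inside the envelope, so it becomes known at the same moment as the allocation. If the person drawing did not like the result for a given patient, the envelope could be closed again, put back and replaced by another. No list position or prior marking would contradict the final record. The person drawing is also the one member of the team who must know verum from placebo.

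At stake is the comparability of the three groups at baseline. Blinding after allocation does not restore it: a blinded assessor measures unequal groups accurately, but they remain unequal. The planned primary analysis is a one-way ANOVA on change in sural SNAP with no covariate named, so the analysis as stated would not adjust for a prognostic imbalance. The Background presents the trial as one of strict methodological standards, and verifiable allocation is part of that.

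**Working it through.** **The plan's own figures (background only).** Inputs from Sample size calculation: difference 1 μV, SD 1.83 μV, alpha 0.05, power 0.8. A two-sided two-sample t-test needs 53.5, so 54 per arm (power at 54 is 0.803). With 10% drop-out, 54 / 0.9 = 60 per arm, 180 in total. The stated numbers reproduce, and nothing below changes them.

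**Which step each safeguard protects.**
- No communication about allocation: acts after the draw.
- Blinded assessor: acts at outcome measurement.
- Pseudonym codes: act in data processing. As the code is inside the envelope, it cannot fix which envelope a patient should receive.
- Closed envelopes: hide the content until opening, but do not record that opening happened.

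None of them covers the interval between opening an envelope and recording the allocation.

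**Can counting reveal a redraw?** There are two cases.
- Envelope discarded: one code is never used and the total falls short of 180. This is detectable.
- Envelope re-closed and returned: it is used later for someone else. When all 180 are used, the arms contain 60/60/60 by construction. This is not detectable by counting.

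**Illustration of the second case.** A 60/60/60 deck was simulated 1,500 times per setting. A draw was called unfavourable if a patient with below-average prognosis drew an active arm, or one with above-average prognosis drew placebo. The expected number is 180 × (1/2 × 2/3 + 1/2 × 1/3) = 90. A share q of these, which is an assumption, was returned and redrawn once.

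| q | mean redraws | mean imbalance, active minus placebo (SD units) | final counts |
|---|---|---|---|
| 0% | 0 | 0.00 | 60/60/60 |
| 10% | 9 | 0.09 | 60/60/60 |
| 20% | 18 | 0.16 | 60/60/60 |
| 50% | 45 | 0.39 | 60/60/60 |

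The imbalance varies from run to run with an SD of about 0.16. The 10% and 20% settings are thus no larger than ordinary chance variation, while the 50% setting is about 0.39 / 0.16 = 2.4 such SDs and could stand out.

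**A hypothetical shift on the primary endpoint.** Assume three of 60 patients are exchanged each way between needle and placebo (six in all), and that those exchanged differ by 2 μV in expected change. Each arm moves by 3/60 × 2 = 0.1 μV in opposite directions, so the difference moves by 0.2 μV. The standard error at 54 per arm is 1.83 × √(2/54) = 0.352 μV, and 0.2 / 0.352 = 0.57. For an unadjusted comparison, the favourable-side error rises from 2.5% to 1 − Φ(1.96 − 0.57) ≈ 8%. Both assumptions are mine, and the 2 μV exceeds the full SD of 1.83 μV.

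**Would small blocks help?** The nurse who opens the envelopes knows all past allocations. Guessing the least-used arm (chance 33%; 3,000 simulated sequences; block sizes assumed) is correct this often:

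| Scheme | all 180 | last 10 |
|---|---|---|
| one set of 180 | 39% | 60% |
| blocks of 3, 6, 9 | 55% | about 57% |
| blocks of 6, 9, 12 | 53% | about 54% |

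One set of 180 is less predictable overall. Blocks are better only over roughly the last 10 draws.

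**The case against.** The strongest reply is that this is a journal article. Opacity, seals, outer numbering, a log and a custodian may all stand in the full protocol, and their absence here is not a defect. That is right for those details. It does not dispose of the point, because the article positively fixes a lottery drawn by the unblinded nurse. A log could be added to that, but while the draw is a lottery there is no prescribed order to check it against.

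Much else in the reply stands. The envelopes are closed, and the draw takes place after recruitment, just before the first session. Nurse 1 is not said to recruit, to judge eligibility or to assess outcomes, and the neurologists who assess patients take no part in other study procedures. The remaining risk is a deliberate redraw, not selective enrolment. Nothing suggests that nurse 1 sees nerve conduction data or could predict the change in sural SNAP.

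A reader might infer more than the text supports:
- That the envelopes are unnumbered. This follows only by inference from their being identical, with the code inside and a lottery draw; it is not stated.
- That nurse 1 keeps a running tally, or meets the patient before the draw. Neither is in the document.
- That every redraw is untraceable. A discarded envelope would leave an unused code and a shortfall.
- That a resulting bias could never be seen. A gross imbalance in a recorded variable could appear in the planned baseline comparison.
- That subjective endpoints are especially exposed. A redraw shifts prognosis and has no particular link to them.
- That predictability near the end of the 180 is a major weakness. It is a small tail effect.

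**Conclusion.** The point holds in a limited form. With the procedure as described, adherence to the random draw cannot be verified, and an envelope re-closed and returned would escape any count of envelopes or arms. This rests on reading the lottery as having no fixed opening order and on the code being inside the envelope.

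It does not follow that concealment failed or that any envelope was redrawn; the document contains no sign of either. No bias can be estimated from it. The 0.2 μV shift and the imbalances of 0.09 to 0.39 SD show what assumed misconduct would do, not what is expected. Sample size, endpoints and analysis are unaffected. The change should be made because it is cheap and the weakness lies at the base of the randomized comparison, but it is no ground for calling the trial invalid.

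**What to change.** Have someone outside the treatment team generate one 1:1:1 list by computer for all 180 patients and transfer it to sequentially numbered, opaque, sealed envelopes. Nurse 1 can still open them, but writes the patient identifier and date on the next envelope before opening and opens strictly in order. At the end, reconcile the used envelopes against the list. Small blocks are not needed: with an unblinded person opening the envelopes they raise overall predictability. A single list leaves the last few allocations partly guessable, as the lottery already does, but with a fixed, pre-marked order a guess gives no opportunity to exchange envelopes unnoticed.

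The Timelines section says that recruitment started in August 2011 and data collection in January 2012. For patients already randomized by lottery, reconcile the used and unused envelopes and codes against the 180, and report that the order of the draw could not be audited. This check can find discarded envelopes, not returned ones.

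The cost is a one-off preparation of list and envelopes, plus a log. No additional treating staff are needed.

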## Blinding

A single-blind design is performed for needle acupuncture because of the difficulties of practitioner blinding for the needling procedure as specified above. A double-blind design is performed for laser acupuncture. Caregiver blinding for laser acupuncture is achieved by dividing the treatment into three steps.i.practitioner fixes the laser needles without activating them;ii.study nurse 1 operates the laser device according to the randomization (verum or placebo);iii.study nurse 2 removes the laser needles after treatment.

Practitioners and study nurses do not communicate concerning the patients’ group allocation. Further, the investigator performing the neurological assessment and NCS does not know about the type of treatment given to the patient.

Regarding patients and the blinding procedure: the laser device is placed behind a folding screen so patients cannot see it. Patients wear laser protective glasses which make it impossible to perceive the laser light. They are informed that the laser device would emit visible and/or invisible laser beams and that the protection of the eyes is fundamental in any case because of the safety precautions as required by law. The laser needles are covered with a blanket. Acoustic functions of the laser device are deactivated prior to the study, so there is no difference between verum and placebo activation. This protocol will not be published in advance so patients cannot draw any conclusions concerning treatment allocations. Study participation is allowed only once.

For data transfer and processing, pseudonym codes are used in order to mask patient identity and treatment groups from outcome assessors and statisticians. The data is only matched after completion of statistical analysis.

